## Abstract

**Background:**

Patients with primary cutaneous melanomas that are ulcerated and >2 mm in thickness, >4 mm in thickness and those with nodal micrometastases at diagnosis, have few options for adjuvant treatment. Recent studies have suggested a role for vitamin D to delay melanoma recurrence and improve overall prognosis.

**Methods/Design:**

This is a pilot placebo-controlled randomised phase II trial to assess the feasibility, safety and toxicity of an oral loading dose of Vitamin D (500,000 IU) followed by an oral dose of 50,000 IU of Vitamin D monthly for 2 years in patients who have been treated for cutaneous melanoma by wide excision of the primary. Patients aged 18 – 79 years who have completed primary surgical treatment and have Stage IIb, IIc, IIIa (N1a, N2a) or IIIb (N1a, N2a) disease are eligible for randomisation 2:1 to active treatment or placebo. The primary endpoints are sufficiency of dose, adherence to study medication and safety of the drug. The secondary endpoints are participation and progression free survival. The study has been approved by the Ethics Review Committee (RPAH Zone) of the Sydney Local Health District, protocol number X09-0138.

**Discussion:**

Effective, non-toxic adjuvant therapy for high risk primary melanoma is not currently available. Favorable outcomes of this phase II study will form the basis for a multi-centre phase III study to assess whether the addition of oral high-dose vitamin D therapy in patients who have completed primary treatment for melanoma and are at high risk of recurrence will:prolong time to recurrence within 5 yearsimprove overall survival at 5 years andbe both safe and tolerable.

62 patients have been randomised since the study commenced in December 2010. Target accrual for the study has been met with 75 patients randomised between December 2010 and August 2014.

The Mel-D trial is conducted by the Australia and New Zealand Melanoma Trials Group (ANZMTG 02.09)

**Trial registration:**

Australia and New Zealand Clinical Trials Registry (ANZCTR) ACTRN12609000351213

## Background

Cutaneous melanoma (CM) is the fourth most commonly diagnosed cancer in Australia, with an incidence of 61.7 cases per 100,000 men, and 40.0 cases per 100,000 women in 2009. There are more than 12,500 new cases of melanoma diagnosed in Australia every year and the diagnosis rates have doubled in the past 20 years. CM is the sixth most common cancer in the United States, with an incidence of 21.3 per 100,000 per year (with an incidence of 35.8 cases per 1000,000 in men and 24.5 cases per 100,000 in women in 2011) [1]. Melanoma makes up only 2.3% of all skin cancers but is responsible for 75% of skin cancer deaths. It is also the most common form of cancer for people aged 15 to 44 years in Australia and accounts for more cancer related deaths in 20–34 year-olds Australians than any other cancer [2].

Since the mid-1960s, CM incidence has risen 3-8% per year in people of European background, with the greatest increases in elderly men [3]. Although there has been progressive improvement in 5 year survival, which is now greater than 85%, CM causes disproportionate mortality in those of young and middle age. Patients with ulcerated tumors thicker than 2 mm, with tumors thicker than 4 mm or with nodal micro-metastases at diagnosis (AJCC Stages IIb, IIc, IIIa (N1a, N2a) and IIIb (N1a, N2a); Tables 1 and 2) have a relatively poor prognosis with no known effective non-toxic adjuvant treatment available.

**Table 1 Tab1:** **TNM classification for CM (3)**

Classification	Thickness (mm)		Ulceration status/Mitoses
Tis	N/A	a	N/A
T1			Without ulceration and mitosis <1/mm^2^
		b	With ulceration or mitosis ≥1/mm^2^
T2	1.01-2.00	a	Without ulceration
		b	With ulceration
T3	2.01-4.00	a	Without ulceration
		b	With ulceration
T4	>4.00	a	Without ulceration
		b	With ulceration
N	No. metastatic nodes		Nodal metastatic burden
N0	0	a	N/A
N1	1 node involved		Micrometastases*
	1 node involved	b	Macrometastases†
N2	2-3 nodes involved	a	Micrometastases
	2-3 nodes involved	b	Macrometastases
		c	Intransit metastases/ satellites without metastatic nodes
N3	4+ metastatic nodes or matted nodes or intransit metastases/satellites with metastatic nodes		
M	Site		Serum LDH
M0	No distant metastases		N/A
M1a	Distant skin, subcutaneous or nodal metastases		Normal
M1b	Lung metastases		Normal
M1c	All other visceral metastases		Normal
	Any distant metastasis		Elevated

*Micrometastases are diagnosed after sentinel lymph node biopsy.

†Macrometastases are defined as clinically detectable nodal metastases confirmed pathologically.

**Table 2 Tab2:** **AJCC pathological staging system for CM (3)**

Stage	Primary tumour thickness and ulceration	Lymph node status	Distant metastasis
Stage 0	Tis	N0	M0
Stage IA	T1a	N0	M0
Stage IB	T1b	N0	M0
	T2a	N0	M0
Stage IIA	T2b	N0	M0
	T3a	N0	M0
Stage IIB	T3b	N0	M0
	T4a	N0	M0
Stage IIC	T4b	N0	M0
Stage IIIA	T1-4a	N1a	M0
	T1-4a	N2a	M0
Stage IIIB	T1-4b	N1a	M0
	T1-4b	N2a	M0
	T1-4a	N1b	M0
	T1-4a	N2b	M0
	T1-4a	N2c	M0
Stage IIIC	T1-4b	N1b	M0
	T1-4b	N2b	M0
	T1-4b	N2c	M0
	Any T	N3	M0
Stage IV	Any T	Any N	M1a
	Any T	Any N	M1b
	Any T	Any N	M1c

### Vitamin D

#### Vitamin D physiology

Vitamin D is a fat-soluble seco-steroid, which acts in the maintenance of calcium and phosphate homeostasis predominantly through increasing gut absorption of calcium and phosphate. Vitamin D is derived from 2 sources – endogenous (from synthesis in the skin – vitamin D_3_) and exogenous (dietary or supplements - vitamins D_2_ and D_3_). The substrate, 7-dehydrocholesterol (7-DHC), the penultimate compound in the cholesterol synthesis pathway, accumulates in the epidermis [4, 5]. Ultraviolet B radiation to the skin transforms 7-DHC to previtamin D_3_, which undergoes nonenzymatic isomerisation to form vitamin D_3_. Vitamin D_3_ is transferred into the blood stream by the vitamin D binding protein, an α‒globulin that has a high affinity to vitamin D and its metabolites.

To be physiologically active, vitamin D (either D_2_ or D_3_) must first be hydroxylated to 25-hydroxyvitamin D (25OHD), predominantly in the liver and 25OHD then to 1α,25‒dihydroxyvitamin D (1α,25OHD), predominantly in the kidneys for export into the bloodstream, though many tissues, including skin, have the capacity to produce 1α,25OHD. Figure 1 shows the physiology of vitamin D in detail [6]. However, vitamin D can be activated by other pathways to metabolites which do not raise serum calcium [7].

**Figure 1 Fig1:**
[figure not shown]
**Physiology of vitamin D.**

#### Serum measurement of vitamin D

Serum 1α,25OHD has a very short half-life and is not a good measure of vitamin D status [8]. Serum 25OHD is the main circulating form of vitamin D. It is relatively stable [9], has a long half-life (τ1/2 = 18.9 +/- 3.1 days) [10] and provides the substrate for local production of the active hormone, 1α,25OHD and is therefore considered the best indicator of vitamin D status [11].

#### Vitamin D and mortality

A meta‒analysis of 18 randomised trials of supplementation with vitamin D provided evidence that supplemental doses in the range of 7.5 to 50 μg per day could significantly decrease all‒cause mortality. The summary relative risk for mortality from any cause was 0.93 (95% confidence interval, 0.87-0.99) [12]. The contribution of specific causes of mortality to the reduction in all‒cause mortality remains unknown.

#### Vitamin D and cancer including melanoma

1α,25OHD exerts physiological functions including regulation of growth and differentiation in a broad variety of normal and malignant cells [13–20] including melanoma [21]. The first study to report anti-melanoma activity by vitamin D showed in vitro, that 1α,25OHD inhibits cellular proliferation, and promotes differentiation and apoptosis, all properties compatible with antineoplastic action [22]. A recent study has also shown some novel hydroxyvitamin D analogues inhibit proliferation and colony formation of melanoma cells, similar to 1α,25OHD [7]. Slightly supraphysiological concentrations of 1α,25OHD have major effects on the cell cycle with a general but not complete G0/G1 cycle arrest [23].

Melanoma cells are able to convert the main circulating form of vitamin D, 25OHD, to 1α,25OHD [24], thus increasing the probability that vitamin D might be able to regulate their growth in vivo. This discovery has led to the hypothesis that autocrine or paracrine production of 1α,25OHD could prevent some cancers (e.g., prostate, colon, breast, pancreas, and ovary) and attenuate their progression. Together, these elements support the hypothesis that high serum 25OHD status could decrease the risk of cancer.

At least in part, because sun exposure, particularly intermittent exposure, is a risk factor for melanoma and sun exposure also increases vitamin D synthesis, there are no clear data relating 25OHD concentrations to risk of melanoma [25, 26]. However, there are additional observational data which supports the proposal that the vitamin D system or vitamin D status may affect the risk of melanoma and/or melanoma outcomes. Although the data are by no means entirely consistent, a recent meta-analysis showed that polymorphisms at two sites in the vitamin D receptor were associated with either reduced (Bsm 1 A allele) or increased (Fok 1 T allele) risk of melanoma [27]. Poorer outcomes from melanoma have been shown with melanoma cells that exhibit reduced or complete loss of vitamin D receptors or cytochrome P27B1 (CPY27B1 hydroxylates 25OHD) [28, 29]. Furthermore, in a post-hoc sub-group analysis of the Women’s Health Initiative randomized controlled trial, subjects with a history of non-melanoma skin cancer who were randomized to 1000 mg of elemental calcium and 400 IU of vitamin D per day had a reduced risk of melanoma (HR 0.43: CI0.1-0.90; P_interaction_ = 0.38) [30]. This was not seen in whole group analyses. In terms of outcomes, patients with melanomas surrounded by high solar elastosis [31] and those diagnosed in summer [32] show higher 5-year survival rates. Both of these factors could be related to higher prevailing 25OHD levels, but other interpretations are possible. Melanomas in patients with higher 25OHD concentrations around the time of diagnosis tend to have a lower Breslow thickness [27, 33], which is associated with a more favourable outcome. Furthermore, in observational studies of patients with melanoma, low 25OHD was associated with worse outcomes [34] and low 25OHD at the time of diagnosis was associated with an increased risk of progression and death over the subsequent 5 years [33]. While these findings are suggestive, the only way to determine whether increasing vitamin D status will improve melanoma outcomes is by conducting a randomized controlled trial [35]. However, several issues need to be addressed before a full scale trial is undertaken.

#### Raising 25OHD concentrations

Vitamin D supplements, usually in the form of vitamin D_3_, are used to raise 25OHD concentrations. When given at a standard dose of 25 or 50 μg (1000 or 2000 IU) per day, 25OHD concentrations take approximately 3 months to reach a plateau [36] and compliance with daily dosing is known to be problematic [37]. Bacon et al. suggested a dosing protocol of a loading dose of 12.5 mg (500,000 IU) of vitamin D_3_ followed by a monthly dose of 1.25 mg (50,000 IU) as a way to achieve an early increase in 25OHD concentrations and improve the likelihood of good compliance over the subsequent trial period, without causing hypercalcemia [38]. Although a high yearly dose of vitamin D of 12.5 mg in older women has been reported to be associated with an increase in falls over the subsequent 3 month period [39], no plausible mechanism has yet been determined, so that in the case of melanoma patients at high risk of recurrence, the possible benefits of this dosing regimen appear to outweigh the possible risks.

### Objectives of the present trial

To determine whether administration of a loading dose of oral vitamin D_3_ (500,000 IU) followed by a monthly tablet of 50,000 IU of oral vitamin D_3_ for 2 years following primary treatment of melanoma at high risk of recurrence:achieves maintenance of serum 25 hydroxyvitamin D concentrations above 80 nmol/l in patients who receive active treatmentachieves > 80% adherence to dosing rates during 2 years of study treatmentachieves adequate recruitment rates (75 patients in 2 years from one site)produces no clinically significant difference in hypercalcaemia incidence between the active and placebo groupsproduces no clinically significant difference in renal function between the active and placebo groupsproduces no clinically significant difference in the incidence of renal calculi between the active and placebo groups

#### Primary endpoints

The primary endpoints will be met if the following criteria are achieved:Dose sufficiencyIf the majority of treated patients achieve a serum 25OHD of 80 nmol/l at both 12 and 24 months and the average serum 25OHD for treated patients is > 75 nmol/l at 12 and 24 monthsDose adherenceIf patients take > 80% of the prescribed monthly doseSafetyCalcium [40]■ If the mean serum calcium concentration in each patient is <2.75 mmol/L (11 mg/dL) over the course of the study.■ If there is no increase in the prevalence of hypercalcaemia relative to the baseline prevalence.■ If the urine calcium excretion in each patient is less than 7.5 mmol/24 h OR the mean urinary calcium-creatinine ratio in each patient is <1.0 (when calcium and creatinine are measured in mmol) over the course of the study.■ If there is no increase in the prevalence of hypercalciuria relative to the baseline prevalence.Kidney function■ If there is no greater than a 20% fall in the average estimated GFR [GFR = 186.3 × SerumCr^-1.154^ × age^-0.203^ × 1.212 (if patient is black) × 0.742 (if female) – MDRD formula (21)] over the course of the study.■ If the average eGFR at the end of the study is no more than 20% less in vitamin D treated patients than in placebo treated patients.Renal calculiIf no more than two episodes of renal calculus occurs in vitamin D treated patients during the course of the study.

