### Sample size and randomisation

The design of the study is an optimal two-stage phase II trial using the approach of Simon [41]. Sample sizes are determined separately for the two cohorts. The two cohorts, those receiving vitamin D and those receiving placebo, will be analysed separately. Assuming a lower limit of efficacy of 48% and a regimen activity level of 68%, the study would proceed in two stages. In the first stage, if more than 7 patients with serum 25OHD less than 80 nmol/l are observed in the first 14 patients in the active arm, consideration will be given to either modifying the regimen or stopping the study due to inactivity.

Twenty-five patients (in a 2:1 randomisation) will be accrued to the placebo arm to allow adequate data to estimate concentration of serum 25OHD in an untreated cohort. Thus it is proposed to accrue a total of 75 patients into the study, 50 receiving vitamin D and 25 receiving placebo. These calculations are based on power of 80% with 95% confidence and allow for a modest dropout rate.

Patients will be centrally randomised by the Australian National Health and Medical Research Council (NHMRC) Clinical Trials Centre using a computerised interactive voice response system (IVRS). Patients will be stratified by gender.

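### The simple-majority criterion for dose sufficiency does not fit the Simon design: a true 48% rate would pass in about 19–34% of trials, not at most 5%

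*Protocol article*

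**What the plan says.** Under Primary endpoints, the Protocol article makes the dose-sufficiency criterion on the proportion that "the majority of treated patients achieve a serum 25OHD of 80 nmol/l at both 12 and 24 months". It adds that the mean must exceed 75 nmol/l at both times.

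Under Sample size and randomisation it states: "The design of the study is an optimal two-stage phase II trial using the approach of Simon". The rates follow: "Assuming a lower limit of efficacy of 48% and a regimen activity level of 68%, the study would proceed in two stages". The error rates are given as "These calculations are based on power of 80% with 95% confidence and allow for a modest dropout rate". The active arm is 50 patients.

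The first-stage trigger is "if more than 7 patients with serum 25OHD less than 80 nmol/l are observed in the first 14 patients in the active arm", upon which "consideration will be given to either modifying the regimen or stopping the study due to inactivity". No final-stage cut-off is printed. Under Statistical methods, the percentage of treated patients above 80 nmol/l is to be reported, with no test or cut-off.

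**The concern.** The majority is the only success rule that the article states for the proportion, and it sits just above the 48% that the design treats as inadequate. A Simon design controls its error only through its two boundaries. With a much lower final boundary, the stated 95% confidence no longer describes the decision. Dose sufficiency is the first primary endpoint, and the Abstract says that favourable outcomes will form the basis of a phase III trial. A false pass here would carry an inadequate regimen forward.

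**Working it through.** **Inputs.** From Sample size and randomisation: p0 = 0.48, p1 = 0.68, power 0.80, first stage of 14, active arm of 50. The 95% confidence is read as one-sided alpha 0.05. From Primary endpoints: success means more than half.

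**Reproducing the design.** An exhaustive exact-binomial search for the Simon optimal design gives n1 = 14, r1 = 7, n = 46, r = 27. The trial stops at 7 or fewer responders in 14 and declares success at 28 or more of 46 (60.9%). Exact alpha is 0.0439 and power 0.805. The chance of stopping early at 48% is 0.662, so the expected sample size is 14 + (1 − 0.662) × 32 = 24.8. The first stage equals the printed 14, and 46/(1 − 0.08) = 50 fits the active arm with about 8% dropout (an assumption, as no figure is given). One-sided alpha 0.025 (14 becomes 17, n = 59), 90% power (22, n = 59) and the minimax design (20, n = 40) do not fit.

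**The printed first-stage rule.** Concern arises at more than 7 failures, that is, at 6 or fewer responders (r1 = 6). This is one patient looser than the optimal r1 = 7, and its wording makes the stop discretionary.

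**Probability of passing.** For final cut-off c of n:

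P(pass | p) = Σ over x = r1+1 to 14 of b(x; 14, p) × P(Bin(n − 14, p) ≥ c − x)

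With no binding stop this is P(Bin(n, p) ≥ c). Each cell shows the pass probability at 48%, then at 68%.

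| Cut-off | No binding stop | Printed stop (r1 = 6) | Simon stop (r1 = 7) |
|---|---|---|---|
| ≥24/46 (majority) | 33.7% / 99.2% | 26.8% / 94.9% | 19.7% / 87.2% |
| ≥26/50 (majority) | 33.5% / 99.4% | 26.3% / 95.1% | 19.2% / 87.3% |
| ≥28/46 | 5.5% / 88.3% | 5.1% / 86.0% | 4.4% / 80.5% |
| ≥30/50 | 6.0% / 91.2% | 5.5% / 88.5% | 4.6% / 82.4% |
| ≥29/46 | 2.9% / 81.1% | 2.7% / 79.5% | not needed |
| ≥31/50 | 3.3% / 85.5% | 3.1% / 83.4% | not needed |

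**The condition on the mean.** If values are roughly symmetric (assumption) and 48% exceed 80 nmol/l, the mean is about 80 − 0.05 × SD. For an SD of 15 to 35 nmol/l (assumption) that is about 79.2 to 78.2, already above 75. Simulation over these SDs, with correlation 0.3 to 0.9 between the two times, changed the pass rates by less than one percentage point.

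**If 48% is meant per time point.** With 48% at each visit and a majority required at each, simulation gives about 14–23% with no stop, 11–18% with the printed stop and 8–14% with Simon's stop.

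**The case against.** Four points on the other side deserve weight.

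- **The boundary is reconstructed.** The article prints neither 46 nor 28, and a condensed article may leave a final boundary to the full protocol. This stands, and the absence of the boundary is not the fault raised. The fault is that the stated rule conflicts with the stated error rates. That does not depend on 28/46, because the majority rule exceeds 5% at either sample size.
- **The 48% may not refer to both time points.** The sample-size text gives no time, and Quality assurance has efficacy reviewed after the first 14 active patients complete 4 and 12 months. Every figure with a first-stage stop therefore assumes that the first stage uses the same outcome as the final analysis. This stands as an assumption. The per-visit reading lowers the excess but leaves it above 5%.
- **This is a pilot with several criteria.** A reader might infer that a majority alone opens phase III. The document does not support that: adherence and safety criteria also apply, and the percentage will be reported for anyone to compare with 48%. The stated error rate of this criterion is still wrong.
- **Inserting 28/46 may look sufficient.** A reader might set 26–34% for the majority against 4.4% for 28/46 and take that cut-off as the whole remedy. That comparison mixes first-stage rules. The 4.4% needs a binding r1 = 7, under which the majority passes 19–20% of the time. Under the printed or a non-binding stop, 28/46 and 30/50 give 5.1–6.0%.

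A single-stage confidence bound does not settle the matter either. The exact one-sided 95% lower bound for 26/50 is 39.5%, which does not exclude 48%, but the bounds for 28/46 (47.7%) and 30/50 (47.4%) also fall just short.

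**Conclusion.** The concern holds. The majority criterion is incompatible with the design that sizes the active arm. It is a wrongly fixed rule, not a missing detail. At a true 48% rate of reaching the level at both times, the regimen would be declared sufficient in 19–20% of trials with Simon's first-stage boundary enforced, 26–27% with the printed rule enforced, and about 34% if the stop is only considered, against at most 5%.

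These figures assume 46 or 50 evaluable active patients, one-sided alpha, and a first stage judged on the same outcome. The document does not support a single figure at the upper end, because the result depends on how the first stage was handled. Nor does it state a 60% threshold; that is inferred from the matching first stage.

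**What to change.** Replace the majority by a final cut-off that keeps one-sided alpha at or below 5% against 48%, for the actual evaluable number and the first-stage rule actually used, and make the two sections agree. Two versions work:

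- At least 28/46 (or 30/50) with a binding stop at 7 or fewer responders in 14: alpha 4.4% (4.6%), power 80.5% (82.4%).
- At least 29/46 (alpha 2.7–2.9%, power 79.5–81.1%) or at least 31/50 (alpha 3.1–3.3%, power 83.4–85.5%), keeping the printed or a non-binding first-stage rule.

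As the article reports accrual complete, the first version is open only if that stop was the one applied. State also that 48% and 68% refer to reaching 80 nmol/l at both 12 and 24 months, and report the proportion with an exact confidence interval.

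The change takes a few sentences and no extra patients. The price is a stricter bar: power of about 80–85%, against about 95% for the majority under the printed first-stage rule. With 29/46 and the printed stop, power falls marginally below 80%.

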### Statistical methods

Analysis of primary endpointsThe percentage of patients achieving a serum 25OHD above 80 nmol/l at 12 and 24 months receiving treatment will be reported. Summary statistics of serum 25OHD concentrations will be reported for both groups at 12 and 24 months.Dose adherence will be reported as the percentage of dose taken compared to the prescribed monthly dose as calculated from the patient diary and study forms. A 95% confidence interval will be reported to check if the expected rate of 80% dosage of study tablets for the duration of the study protocol by all patients is obtained.Safety outcomes will be reported as the proportions of patients exceeding the following maxima, as well as summary statistics where appropriate.Analysis of secondary endpointsParticipation rate will be reported as the proportion of subjects eligible and invited to participate who agree to be randomised. A 95% confidence interval will be reported to check if the expected rate of 60% was obtained.Progression free survival will be displayed using Kaplan-Meier survival curves.

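### The end-of-study kidney criterion, and on its natural reading the 20% fall criterion, uses unadjusted group averages, so marked eGFR decline in a minority can be averaged out

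*Protocol article*

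**What the plan says.** The Primary endpoints section of the protocol article lists the criteria under which the safety endpoint counts as met. Two concern kidney function:

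- **Criterion 1** is met "If there is no greater than a 20% fall in the average estimated GFR" over the course of the study. No arm is named.
- **Criterion 2** is met "If the average eGFR at the end of the study is no more than 20% less in vitamin D treated patients" than in placebo patients.

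Other safety items in the list work at patient or event level. The serum calcium item begins "If the mean serum calcium concentration in each patient is <2.75 mmol/L", and the urine calcium item likewise sets a limit for each patient. Two further items concern the prevalence of hypercalcaemia and hypercalciuria. Renal calculi are counted, with at most two episodes allowed in vitamin D patients.

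On reporting, Statistical methods says: "Safety outcomes will be reported as the proportions of patients exceeding the following maxima", with summary statistics where appropriate. No list of maxima follows in the article. Table 3 schedules eGFR at baseline, 8, 16 and 24 months. The planned arms are "50 receiving vitamin D and 25 receiving placebo".

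**The concern.** A group average shows whether eGFR shifts in the arm as a whole. It is insensitive to a large loss in a few patients, because unaffected patients dilute it. The list recognises this for calcium and calculi, where it looks at patients or counts events, but not, as worded, for eGFR.

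Safety is a primary endpoint, and the Abstract says that favourable results will be the basis for a phase III trial. A kidney criterion recorded as met could then be carried forward although a sizeable minority of treated patients had declined markedly. Eligibility requires eGFR within the laboratory's normal range (Appendix 1), so such declines would be real losses from normal.

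Criterion 2 has a second weakness. It compares end-of-study values without reference to where each arm began. With 50 and 25 patients, and randomisation stratified only by gender, a chance difference in baseline eGFR passes straight into the comparison.

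**Working it through.** **Inputs.** Both 20% limits are inclusive (Primary endpoints). The arms are 50 and 25 (Sample size and randomisation). The losses, drifts and baseline values below are illustrative assumptions; the article gives no eGFR data.

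**1. The denominator.** An exact search for the optimal two-stage design with rates 0.48 and 0.68, one-sided alpha 0.05 and power 0.80 gives a first stage of 14 and a total of 46 (alpha 0.0439, power 0.805). Then 46/(1 − 0.08) = 50. The stated arm size is therefore reproduced if the unspecified modest dropout is about 8%, which is an assumption.

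**2. Formula.** If k of n patients lose a fraction L, the others lose a fraction d, and baselines are equal, then

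fall in average = [k × L + (n − k) × d] / n.

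**3. Main case.** With n = 50, k = 10, L = 0.5, d = 0: 10 × 0.5/50 = 10%. Criterion 1 is met. With placebo unchanged, the vitamin D average is 10% below placebo, so criterion 2 is met.

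This case is not close to the limit:

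- Others drift down 5%: (10 × 0.5 + 40 × 0.05)/50 = 7/50 = 14%, met.
- Others drift down 10%: (5 + 4)/50 = 18%, met.
- Affected patients start at 100, others at 80: baseline average (10 × 100 + 40 × 80)/50 = 84; loss 10 × 50/50 = 10; 10/84 = 11.9%, met.

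**4. Limiting case.** With L = 0.5 and d = 0, k × 0.5/50 ≤ 0.20 gives k ≤ 20. So 19 gives 19% (met), 20 gives exactly 20% (met because the limit is inclusive) and 21 gives 21% (not met). The largest passing number at other losses is:

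| Loss in affected patients | Largest k of 50 | Fall in average |
|---|---|---|
| 25% | 40 | 20.0% |
| 40% | 25 | 20.0% |
| 50% | 20 | 20.0% |
| 75% | 13 | 19.5% |

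**5. How fragile the limit of 20 is.**

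- Others drift down 5%: 0.5k + 0.05(50 − k) ≤ 10, so k ≤ 16. At 10% drift, k ≤ 12.
- Baselines of 80 (20 affected) and 100 (30 others): average 92, loss 20 × 40/50 = 16, fall 16/92 = 17.4%, met. With the baselines reversed: average 88, loss 20, fall 20/88 = 22.7%, not met.
- If 45 or 40 patients are analysed, 18 or 16 may be halved, still 40%.
- If criterion 1 pools both arms, 20 halved gives 20 × 0.5/75 = 13.3%, so the limit lies further off.
- If placebo falls 5% or 10% and the unaffected vitamin D patients do not change, criterion 2 alone tolerates 1 − 0.01k ≥ 0.8 × 0.95 (k ≤ 24) or ≥ 0.8 × 0.90 (k ≤ 28).

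**6. Baseline imbalance.** Suppose the vitamin D arm starts at 110 and ends at 80, and placebo stays at 100. Criterion 2 sees 80 against 100, exactly 20% less, and is met, although the vitamin D arm has lost 30/110 = 27%. Criterion 1 fails if it refers to the vitamin D arm. If it pools both arms, the average goes from 8000/75 to 6500/75, a fall of 1500/8000 = 18.75%, and it is met. Which arm criterion 1 covers therefore decides the outcome.

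**The case against.** **Criterion 1 may not be a group average.** It names no group, and the per-patient calcium item ends with the same reference to the course of the study, so an average over time within a patient is possible. This stands as an ambiguity. The per-patient wording of the calcium items is absent here, which favours the group reading, but that is an inference. Criterion 2 is not open to this doubt.

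**Per-patient reporting is promised.** Statistical methods speaks of proportions of patients, and a permitted fall of 20% could be regarded as a maximum. A reader might infer that no per-patient renal outcome is planned at all. The article does not support that, because the announced list is not shown. What can be said is that the passage concerns reporting and adds no per-patient decline to the success rule.

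**Other safety criteria cover part of the pathway.** Kidney damage through calcium toxicity would probably also breach the calcium or calculus criteria. This stands in part and lowers the stakes, but those criteria do not measure eGFR decline itself.

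**Individual oversight exists.** A medical monitor is told of results considered clinically significant, and a committee reviews safety (Table 3 notes; Quality assurance). A reader might infer that severe decline would go unseen; the article does not support that either. But oversight does not enter the endpoint. The eGFR entry under Dose cessation in Appendix 2 is worded as a value above the normal range, so it does not capture a fall and must be reconciled with the kidney criteria.

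**The objective is itself framed between groups.** This is true, so it would be too strong to say that averages cannot address it. Whether 20% is the right limit is a clinical judgement on which the article gives no basis for another figure.

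**Conclusion.** The point holds as a cheap improvement. For criterion 2 it follows directly from the wording; for criterion 1 it holds on the natural reading. The illustration to rely on is 10 of 50 patients with halved eGFR: the average falls 10%, and it stays under 20% if the remaining patients drift down by 5% or 10%.

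A reader might take 20 of 50 as the general tolerance. It is only the boundary case. It rests on inclusive limits, equal baselines and no change in the other 30 patients or on placebo; 21 would fail, and modest drift lowers the number to 16 or 12. Nothing in the article suggests that losses of this size are expected. The gap lies in what the success rule can detect, not in the whole of the trial's safety oversight.

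**What to change.** 1. Keep both average criteria and state which arm criterion 1 refers to.
2. Report alongside them, by arm, the number and proportion of patients whose eGFR falls more than 20% from their own baseline at 8, 16 or 24 months, with the difference between arms and its exact 95% confidence interval. The 20% is the protocol's own figure, used here for reporting and not as a treatment rule. The placebo arm shows how often such a fall occurs without vitamin D.
3. Compare mean end-of-study eGFR between arms adjusted for baseline eGFR, with a 95% confidence interval.

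The cost is small: one more table and one adjusted comparison from values already scheduled, with no new visit or assay. When the article was written 21 patients had completed 24 months, so this could be specified before the final analysis. The downside is that the renal safety claim becomes somewhat harder to support, and with 50 and 25 patients the interval for the difference in proportions will be wide.
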